### Randomisation

Subjects will participate in two study sessions (day 1 and day 2), in which the participants will receive either SHAM stimulation or verum stimulation (cross-over design; stimulation will be counterbalanced across sessions). The respective stimulation condition in the first session will be determined using a lottery procedure (online randomisation tool). In summary, each participant will switch from verum to SHAM and vice versa.

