#### Baseline assessment

At the beginning, a medical interview will be conducted in which the relevant epidemiological and demographical data, including age and sex, are collected. Following the interview, a neuropsychological examination will be carried out, consisting of SDMT, BDI-II, FSMC and EDSS (the latter only used in PwRRMS).

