#### Intervention

After baseline assessment, consisting of neuropsychological assessment (duration: about 30 min), stimulation (SHAM stimulation or verum stimulation) will be applied for 15 min followed by a second neuropsychological assessment under stimulation. In the first 15 min of stimulation (SHAM stimulation or verum stimulation), the participant will sit relaxed in a chair without a specific task. When the second neuropsychological assessment is completed, taVNS will be applied for another 5 min without a specific task.

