#### Follow-up and further investigations

There will be a wash-out period of at least 7 days to eliminate possible long-term effects of stimulation. The second assessment on study day 2 will follow the same protocol as study day 1.

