#### Data analysis

Statistical analysis will be conducted using SPSS Statistics V.25 (IBM SPSS Statistics for Mac, V.25.0. Armonk, NY: IBM Corp). With a total number of n=30 in each study arm, a normal distribution can be assumed. Based on this, normally distributed variables will be presented as mean±SD. Non-normally distributed variables will be presented as median and (IQR). A linear mixed model will be performed for the primary/secondary outcomes using ‘time’ (pre vs during), ‘stimulation’ (taVNS vs sham), ‘group’ (MS vs controls), ‘session order’ (Session 1 vs Session 2) and ‘control variables’ (age, fatigue, depression and severity) as fixed, ‘participant’ as random effects. A significance level of 5% will be used to test the hypotheses.

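### With participant as the only random effect, the listed stimulation test is anti-conservative and a change test loses power if SDMT level varies by session; the same-session pre-score is better used as a covariate

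*Protocol article*

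**What the plan says.** The Randomisation section sets up a two-period cross-over: "Subjects will participate in two study sessions (day 1 and day 2), in which the participants will receive either SHAM stimulation or verum stimulation". Within a session, the Baseline assessment comes first: "a neuropsychological examination will be carried out, consisting of SDMT, BDI-II, FSMC and EDSS". The Intervention section then states that "stimulation (SHAM stimulation or verum stimulation) will be applied for 15 min followed by a second neuropsychological assessment under stimulation". Under Follow-up and further investigations, day 2 repeats the day 1 protocol after a gap: "There will be a wash-out period of at least 7 days to eliminate possible long-term effects of stimulation". This makes four SDMT scores per participant, in two pairs taken on different days.

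The Data analysis section fixes the model: "A linear mixed model will be performed for the primary/secondary outcomes using ‘time’ (pre vs during), ‘stimulation’ (taVNS vs sham"), followed by group, "session order’ (Session 1 vs Session 2") and the control variables age, fatigue, depression and severity. These enter as fixed effects, and the text ends with the random part and the test level: "participant’ as random effects. A significance level of 5% will be used to test the hypotheses". No session-within-participant term, residual covariance or time-by-stimulation interaction is named. The pre-stimulation SDMT appears only as one level of the time factor.

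The primary outcome is SDMT in PwRRMS, sham versus verum. One secondary outcome refers to the difference in change between groups.

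**The concern.** A single participant effect gives all four scores the same correlation. In practice, two tests in one sitting may share whatever is particular to that person on that day. The fixed session term removes only the average shift from day 1 to day 2, not each participant's own departure from it.

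Stimulation is assigned to whole sessions, so a comparison of session levels carries the session variance in full, while a within-session change carries none of it. Pooling both sources into one residual gives the wrong error term for each, in opposite directions. At stake are the nominal 5% level if the stimulation main effect is read, and power if the change is read. The protocol itself concedes that 30 per group may be too few for smaller effects.

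Treating the pre-score only as an outcome row also means that, as the model is written, it is not used to explain variation in the during score from the same session.

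**Working it through.** **Plan's own figure.** There is none to reproduce. The Sample size section gives 30 per group without effect size, SD, within-person correlation or power. For orientation, 30 paired differences give 80% power at two-sided 5% for a standardised difference of (1.960 + 0.842)/√30 = 0.51.

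**Inputs.** From the protocol: two sessions, two SDMT scores per session, 30 PwRRMS, 5% level (taken as two-sided). Assumed: score = participant effect + session-within-participant effect (variance s) + test error (variance e), with r = s/e from 0.1 to 2. Set e = 1.

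**Residual used by the participant-only model.** Of the three within-participant degrees of freedom, one lies between sessions (mean square 1 + 2r) and two lie within sessions (mean square 1). The pooled value is m = (1 + 2r + 2)/3 = 1 + 2r/3.

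**Variance of each verum-sham contrast, per participant.**
- Main effect (mean of both tests): true 1 + 2r, model m.
- During test only: true 2(1 + r), model 2m.
- Change (during minus pre): true 4, model 4m.

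With k = model SE/true SE, type I error is 2[1 − Φ(1.96k)]. The power of a change test that has 80% with the right error becomes Φ(2.80 − 1.96k).

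| r | k main | Type I main | k during | Type I during | k change | Type I change | Change power |
|---|---|---|---|---|---|---|---|
| 0 | 1.00 | 5.0% | 1.00 | 5.0% | 1.00 | 5.0% | 80% |
| 0.1 | 0.94 | 6.5% | 0.98 | 5.4% | 1.03 | 4.3% | 78% |
| 0.25 | 0.88 | 8.4% | 0.97 | 5.8% | 1.08 | 3.4% | 75% |
| 0.5 | 0.82 | 11.0% | 0.94 | 6.5% | 1.15 | 2.4% | 71% |
| 1 | 0.75 | 14.4% | 0.91 | 7.4% | 1.29 | 1.1% | 61% |
| 2 | 0.68 | 18.1% | 0.88 | 8.4% | 1.53 | 0.3% | 42% |

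Example, r = 0.5: m = 1.333; main-effect k = √(1.333/2) = 0.816; 2[1 − Φ(1.60)] = 11.0%.

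Simulation with 20,000 trials at n=30 agrees: at r = 0.5, k is 0.815 (type I 10.7%) for the main effect and 1.152 (2.5%) for change. With both groups, n=60, k is 0.813 and 1.155.

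**Adding a session-within-participant effect** (150 simulated data sets, REML, n=30, r = 1). The mean SE for the main effect moves from 0.235 to 0.316 (empirical SD 0.340), and for change from 0.470 to 0.363 (empirical SD 0.349).

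**Same-session pre-score as covariate.** The verum-sham difference in during scores, adjusted for the difference in pre-scores, has variance 2(1 + r)(1 − ρ²) with ρ = r/(1 + r). The correctly specified change contrast has variance 4. Power below is simulated at n=30 for a during-test effect of 2.80 × 2/√30 = 1.02 residual SDs. That effect gives 80% for change by the normal approximation and about 77% with the t distribution.

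| r | Adjusted variance | Cut against 4 | Power, change with right error | Power, covariate |
|---|---|---|---|---|
| 0.1 | 2.18 | 45% | 77% | 95% |
| 0.25 | 2.40 | 40% | 77% | 93% |
| 0.5 | 2.67 | 33% | 77% | 90% |
| 1 | 3.00 | 25% | 77% | 86–87% |
| 2 | 3.33 | 17% | 77% | 83% |

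The covariate analysis held type I error at about 5% throughout.

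**The case against.** **An unseen analysis plan may specify a residual covariance.** In a mixed model this is set separately from the random effects, and a suitable within-session structure would remove the error-term problem. That limits any statement about what the trial will finally do. It does not cure the text: the article states the random part explicitly and gives the pre-score no role other than a level of time.

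**The size is assumed.** This stands. The protocol gives no session variance, and testing each participant at a constant time of day should hold it down. Fatigue and depression, if entered as re-measured at each session, could absorb some of it, although the protocol describes the fatigue scale as measuring trait fatigue. At r = 0.1 the distortion is small; at r = 0 there is none.

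**The largest type I error belongs to an ill-matched contrast.** This also stands in part. The stimulation main effect averages in a score taken before stimulation starts. A during-only contrast is far milder, and a change contrast carries no excess false-positive risk. But no interaction is listed, so the main effect is what the model tests as written.

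A reader might infer that the planned standard errors are definitely wrong, or that the trial runs at an 18% type I error. The documents support neither. The first needs positive session variance and no within-session covariance; the second also needs r = 2 and the main-effect reading.

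**The covariate analysis is a preference.** A four-row model with correct covariance and a common pre-stimulation mean would also recover the information in the pre-score. True, but the listed model is not that model, and the gain uses data already collected.

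**Conclusion.** The point holds conditionally. The direction of both errors follows by algebra for any positive session-within-participant variance, with independent test errors and no within-session covariance in the model. Their size depends on a ratio that the documents do not give. Over an assumed 0.1 to 2, the stimulation test as listed runs at about 6.5% to 18% instead of 5%, a during-only contrast at about 5.4% to 8.4%, and a change test loses between about 2 and 38 percentage points from 80% power.

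The gain from using the pre-score as covariate does not depend on the error-term fault and is greatest where that fault is smallest. This is a specification that should be changed; it is not evidence that the result will be invalid.

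**What to change.** Make the during-stimulation SDMT the outcome, two rows per participant. Use the same-session pre-stimulation SDMT as covariate, stimulation and session as fixed effects, and participant as random intercept. Split the covariate into the participant's mean pre-score and the session's deviation from it, so that the between-person slope does not contaminate the within-person adjustment. Equivalently, regress the verum-sham difference in during scores on the difference in pre-scores and on sequence.

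If the four-row model is kept, add a session-within-participant random effect or an equivalent within-session covariance. This corrects the standard errors but does not by itself give the covariate gain. The contrast that tests the primary outcome should then be named, because the three candidates behave differently.

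The cost is analysis wording and a few denominator degrees of freedom. In the difference regression for PwRRMS, 30 − 3 = 27 remain, against 30 − 2 = 28 for a change-score analysis with sequence. No new data are needed, and the change can be made before any comparison by stimulation is seen.

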## Discussion

taVNS is an already established non-invasive treatment option for depression or epilepsy.^51^,^53^ Recent studies investigating the effect of taVNS on cognition in healthy subjects provide preliminary evidence for its potential to also improve cognitive functions (eg, improvement of executive functions and spatial working memory).^23 24^

Mechanistically, taVNS might mediate its effect on cognition via different neurotransmitter systems and thus be a promising treatment option for cognitive impairments.^14 21^ For example, taVNS leads to an activation of the NTS which, in turn, leads to a stimulation of the locus caeruleus (release of norepinephrine).^54 55^ The increased levels of norepinephrine have widespread effects on cerebral structures that are important for different cognitive functions (eg, enhanced synaptic plasticity in the hippocampus).^56^

Furthermore, fMRI data revealed an anatomical overlap between SDMT performance and areas that are activated through taVNS application.^35^ A neurophysiological activation of these structures (such as the cerebellum or parietal cortical areas) might lead to an alteration in SDMT performance in PwRRMS.

Based on these findings, we hypothesise that taVNS will significantly improve processing speed in PwRRMS as well as in healthy controls (primary). Moreover, we will assess whether the stimulation-induced effect is also modulated by additional disease variables like disease severity, fatigue or depression (secondary).

To the best of our knowledge, this is the first study investigating the effect of taVNS in non-motor symptoms in PwRRMS (processing speed). With this study, we will determine whether taVNS improves an important aspect of cognitive function, that is, processing speed.

As in any other study, our study protocol has several limitations. First, this is a single centre, SHAM controlled, single-blinded prospective cohort study with a limited sample size of 30 participants in each group. This reduces the external validity of the study and might lead to an insufficient power to detect smaller effect sizes. To reduce interindividual differences, a cross-over design will be used. Secondary SHAM stimulation will be performed at the participants’ earlobe. Neuroanatomically, the earlobe is innervated by the great auricular nerve and not by the vagal nerve.^8^ Further studies revealed that the earlobe might not be a complete neutral SHAM condition, as the earlobe might still have vagal innervation.^57^ Despite the fact that the earlobe stimulation might cause a bias, we use the earlobe-SHAM-stimulation as it is still the standard SHAM stimulation. As there are no previous studies investigating the effect of taVNS on non-motor symptoms in PwRRMS, the optimal stimulation parameters cannot be clearly defined. We therefore use stimulation parameters that were already used to assess non-motor symptoms in other diseases besides multiple sclerosis.

Clinically, taVNS might be used as a new, non-invasive, well-tolerated and safe therapeutic option.^5 7^ A novel therapeutic strategy could enhance treatment modalities for multiple sclerosis and possibly also expand therapeutic options for other neurological disorders. Scientifically, these results may lead to a better understanding of how taVNS affects non-motoric symptoms in PwRRMS.

## Ethics and dissemination

The study protocol was reviewed and approved by the local ethics committee of the University Medical Centre Greifswald (study reference number: BB137/24; study registration: DRKS00034912). The study will be conducted in accordance with the Professional Code of Conduct for Physicians of the Medical Association of Mecklenburg-Vorpommern and the Declaration of Helsinki (V.1996). All collected data will be stored and processed pseudonymously according to currently existing data protection guidelines and laws. Names, examination results and other confidential information of the study participants are subject to medical confidentiality. Third parties do not have access to the original documents. Appropriate exceptions regarding the verification of the conformity of the original data, for example, by the ethics committee, are excluded. The study participants will be informed about the study procedure and potential risks associated with participation in the study. All study participants gave their informed consent before the start of the study.

To ensure data security, data of the participants will be pseudonymised and recorded containing participants IDs. Data will be secured with a password, solely accessible for study staff. Following good scientific practice, data will be stored for at least 10 years. Study results will be disseminated through academic conferences as well as peer-reviewed publications.
